### Case dropout management:

2.10

Participants have a right to withdraw from the study at any time if they feel uncomfortable upon receiving the treatments or being diagnosed with serious complications or diseases. They will then be referred to the preferred department for further treatment and management. If cases of dropout, the researcher need to contact the participant to reason the problem out, collect, and record all the necessary assessments on the last visit as well as the date of last visit. All data available until the date of withdrawal will be stored for further statistical analysis.

### Safety monitoring

2.11

Before randomization, blood will be drawn for routine blood tests and liver and kidney function tests so that patients with severe heart, liver, or kidney diseases can be identified and excluded. The same examinations will be performed again at the end of the study to look for possible side effects (Table 1). Possible acupuncture-related adverse events (e.g., fainting, needle stick injury, local infection, subcutaneous hematoma, and low-grade fever) will be documented. Serious adverse events will be reported to the principal investigator immediately. All unexpected and unintended responses, even those not necessarily related to the acupuncture intervention, will be documented as adverse events.

**Table 1 T1:**
[figure not shown]
Schedule for enrollment, intervention, and assessments.

### Interventions

2.12

All participants will receive 3 treatment sessions per week for 3 consecutive months. The treatment group will receive standardized rehabilitation therapy plus acupuncture; the control group will receive only standardized rehabilitation therapy (Fig. 1).

#### Acupuncture

2.12.1

The acupuncture points will be identified according to the method recommended by the World Health Organization. The area will be sterilized before puncture. Acupuncture needles (25 mm in length and 0.30 mm in diameter) manufactured by Suzhou Huato Medical Instruments Co. Ltd., Suzhou, China, will be used for all patients.

The following acupoints will be used:

1.Local acupoint: Da Zhui (GV14), Sheng Zhu (GV12), Ming Men (GV4), Shen Shu (BL23), Zu San Li (ST36), San Yin Jiao (SP6), and Tai Xi (KI3). The needle will be inserted and removed immediately after manipulation of needle (twisting and rotating manipulation, with neutralizing technique between enforcing and reducing for 2 seconds) is done.2.Scalp acupoints: Si Shen Zhen (1.5 cun superior, inferior, lateral, and medial to GV20; 4 needles in total); Zhi San Zhen (intersection of frontal hairline section with midline of the head, with 3 cun lateral and medial to the midline point; 3 needles in total); Nao San Zhen (1.5 cun lateral and medial to GV17; 3 needles in total); and Nie San Zhen (2 cun above the tip of the ear as the first acupoint, with 1 cun lateral and medial to the current point, on bilateral sides of the head; 6 needles in total). Si Shen Zhen will be needled obliquely 0.8 to 1 cun with the tip of the needle pointing away from GV20; Zhi San Zhen will be needled obliquely 0.5 to 0.8 cun; and Nie San Zhen and Nao San Zhen will be needled obliquely 1 cun inferiorly. Needle insertion will be at an angle of 20° to 30°. No lifting/thrusting manipulation will be done after needle insertion; the needle will be left in situ for 30 minutes. Electrical stimulation will be applied only in patients without history of seizure/epilepsy. The scalp acupoint will be connected to G-6805, an electrical acupuncture stimulation device. A pair of electrodes will be connected to the acupoints on both sides of the scalp, where Si Shen Zhen (the acupoint located lateral or medial to GV20) is connected to Nie San Zhen (the acupoint located directly 2 cun above the tip of the ear) on both sides of the scalp, and continuous waves stimulation will be applied for 30 minutes.

#### Standardized physical rehabilitation

2.12.2

Standardized physical therapy will include comprehensive physical rehabilitation and biofeedback therapy. Patients will attend 3 30-minute rehabilitation sessions per week for a total of 3 months. The physical rehabilitation sessions will be conducted one-to-one in a quiet and safe environment so that the child is relaxed. Parents will be advised to bring the child for treatment in the mornings when their ability to concentrate on tasks will be maximum.

### Outcome assessment

2.13

Outcome will be assessed at baseline, 3 and 6 months after the start of treatment using the modalities and instruments described below. (Table 1)

#### Primary outcome measures

2.13.1

##### Multimodal magnetic resonance imaging (MRI)

2.13.1.1

Multimodal MRI can provide functional and structural information. The comprehensive assessment might contribute to the development of new perspective in terms of the diagnosis, treatment principle, assessment as well as the prognosis of the disease.

##### Ambulatory electroencephalogram (EEG)

2.13.1.2

Conventional EEG directly reflects the functionality of the brain activity,^[9,10]^ but its value is limited in the pediatric age-group, especially in children with CP, as they are unlikely to cooperate during the examination. Ambulatory EEG can record brain waves in various states (e.g., during sleep, physical activity).

##### Gesell Development Diagnostic Schedules (GDDS)

2.13.1.3

The GDDS is widely used in medical research for assessing intellectual development of children aged 0-6 years. It can be used for children with disabilities.

#### Secondary outcome measures

2.13.2

##### Gross Motor Function Classification System (GMFCS):

2.13.2.1

GMFCS reflects the gross motor function of children with CP. It classifies children with CP into 5 different age-groups, with 5 levels in each age-group, according to the childs current motor function. It is a measure of the severity of the childs motor dysfunction.

##### Gross Motor Function Measure (GMFM):

2.13.2.2

The GMFM is widely used to measure changes in gross motor function of children with CP. It assesses 5 different dimensions of the childs motor function: A) lying and rolling (17 items); B) sitting (20 items); C) crawling and kneeling (14 items); D) standing (13 items); and E) walking, running, and jumping (24 items). Each gross motor skill is scored to note its presence or absence (or emergence). Each item is scored on a scale of 0 to 3 (0 = unable, 1 = attempted, 2 = partially accomplished, 3 = completed).

Calculation of dimension percentage scores:

**Figure d38e739:**
[figure not shown]

Goal Total Score: Sum of % scores for each dimension identified as a goal area Number of Goal Areas

##### Functional Independence Measure (WeeFIM):

2.13.2.3

WeeFIM measures a childs consistency in the performance of essential daily functions. Three main domains (selfcare, mobility, and cognition) are assessed by interviewing or by observing a childs performance of a task to criterion standards. WeeFIM is categorized into 2 main functional streams: “Dependent” and “Independent”. The total score can range from 18 to 126 (mobility: 91, cognition: 35), with 126 = completely independent, 108–125 = basically independent, 90–107 = mildly dependent, 72–89 = mildly dependent, 54-71 moderately dependent, 36–53 = severely dependent, 19–35 = most severely dependent, and 18 = completely dependent.

### Statistical methods

2.14

Normally distributed data will be summarized as means (± standard deviation) and non-normally distributed data as medians (range). The Student t test or the Wilcoxon rank sum test will be used to analyze differences between the groups. If there is heterogeneity of variance, then Satterthwaite corrected *t* test will be used. *P* ≤ .05 will be considered statistically significant and *P* ≤ .0.01 will be considered highly significant.

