### Intended sample size

2.4

The following formula was used to calculate the intended sample size considering an average efficiency of 92% and 63% for the treatment and the control groups, respectively, α = 0.05, and β = 0.2: 

Thus, the estimated sample size for each group is 30. However, assuming a shedding rate of 20%, the sample size would increase by another 20%. Thus, the sample size intended for each group is 36, with a total sample size of 72.

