### Participants

2.5

A total of 72 children with CP will be recruited (36 from each of the 2 hospitals) and randomly assigned to the treatment group or the control group in a ratio of 1:1 (Fig. 1).

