**Figure 1 F1:**
[figure not shown]
Participant flow diagram.

Diagnosis will be according to 2015 China Guidelines Protocol in CP Rehabilitation:^[6]^

Main criteria:

1.Disorder of the central nervous system with persistent motor dysfunctionality2.Abnormality of the development of movement and posture3.Abnormality of muscle tone and muscle power4.Abnormality in muscle reflex

Secondary criteria:

1.Evidence related to etiology of cerebral palsy.2.Present of magnetic resonance imaging (MRI) report

According to the guidelines there are 6 types of CP: spastic quadriplegia, spastic diplegia, spastic hemiplegia, ataxic CP, mixed CP, and dyskinetic CP. Only children with spastic forms of CP will be considered for inclusion in this study.

*Inclusion criteria*:

1.diagnosis of spastic CP,2.age between 6 months and 7 years,3.willingness to participate in the study (parents sign the inform consent form on behalf of their children).

*Exclusion criteria*:

1.severe form of spastic CP or2.presence of a serious comorbidity (e.g., congenital heart disease, hydrocephalus, increased intracranial pressure, psychiatric or psychological disorders, liver or kidney dysfunction, or chronic infectious disease).

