### Randomization

2.9

Enrolled patients will be randomized into the treatment (acupuncture plus standardized rehabilitation) group or the control (standardized rehabilitation alone) group in a ratio of 1:1, using the “sample” function in R (https://cran.r-project.org/). The randomization code will be placed inside sealed and opaque envelopes that will be opened only after recruitment of the patients.

Criteria of dropout:

1.Participant failed to continue the follow-up due to personal reason or unable to cooperate fully during the assessments.2.Being diagnosed with serious complications or diseases.3.Parents/guardian self-requested for termination of the treatment.

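### The plan fixes unadjusted two-sample tests and leaves the tested variable open; adjusting for baseline value and age would gain precision, by an amount the documents do not let us fix

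*Protocol article*

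**What the plan says.** All places are in the protocol article.

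- **Statistical methods (2.14).** "The Student t test or the Wilcoxon rank sum test will be used to analyze differences between the groups". A variant for unequal variances follows: "If there is heterogeneity of variance, then Satterthwaite corrected *t* test will be used". All three tests compare two samples without covariates. The section does not define the variable being tested.
- **Outcome assessment (2.13).** "Outcome will be assessed at baseline, 3 and 6 months after the start of treatment". Each outcome therefore has its own baseline value.
- **Participants (2.5).** Eligibility covers "age between 6 months and 7 years", and recruitment is "36 from each of the 2 hospitals".
- **Randomization (2.9).** Allocation is described thus: "Enrolled patients will be randomized into the treatment (acupuncture plus standardized rehabilitation) group or the control (standardized rehabilitation alone) group in a ratio of 1:1". The allocation is drawn with the R sample function. No stratification by age or severity is stated, and the section does not say whether the draw is made separately within each hospital.

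**The concern.** The children span a 14-fold age range (6 to 84 months). The GMFM items run from lying and rolling to walking, running and jumping, and the WeeFIM covers self-care, mobility and cognition. Such scores can be expected to depend on the child's age and starting level, whatever the treatment. A two-sample test on follow-up scores puts all of that spread into the error term, although the baseline value and age that would explain part of it are already collected.

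Two things are at stake in a trial of 72 children. One is power to detect a moderate effect. The other is how the result reads if the arms happen to differ in age or starting level, because the planned test has no means of adjusting for it. The silence on follow-up score versus change also matters, because the two can give different estimates and standard errors from the same data.

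**Working it through.** **1. The plan's own figure.** Section 2.4 sizes the trial "considering an average efficiency of 92% and 63% for the treatment and the control groups", with "α = 0.05, and β = 0.2", and states 30 per group. The unpooled formula, two-sided, gives

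(1.960 + 0.842)² × (0.92×0.08 + 0.63×0.37) / 0.29² = 7.849 × 0.3067 / 0.0841 = 28.6, so 29 per group.

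The arcsine formula gives 29.1, so 30, and the pooled formula gives 32. The stated 30 therefore reproduces. It is a calculation for response proportions, however, and says nothing about the precision of a t or Wilcoxon comparison.

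**2. Inputs for the precision check.**

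- Per arm: 36 less 20% dropout (2.4) is 36 × 0.8 = 28.8, rounded down to 28.
- r, the correlation between an outcome's baseline and follow-up values: not in the documents; assumed 0.5 to 0.8.
- True difference: not in the documents; assumed 0.5 SD of the follow-up score.
- Two-sided alpha 0.05 (the plan does not state sidedness).

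**3. Formulas.** Take the variance of a raw follow-up comparison as 1, with equal SDs at baseline and follow-up.

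- ANCOVA on baseline: 1 − r²
- Change-score t test: 2(1 − r)
- ANCOVA relative to change score: (1 − r²) / [2(1 − r)] = (1 + r)/2

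Power comes from the noncentral t with noncentrality (0.5/√v) × √(28/2), where v is the relative variance above. Degrees of freedom are 54, less one for ANCOVA.

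**4. Results, 28 per arm.**

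| r | ANCOVA variance saving vs raw follow-up | ANCOVA variance saving vs change score | Power, raw | Power, change score | Power, ANCOVA |
|---|---|---|---|---|---|
| 0.5 | 25% | 25% | 45.1% | 45.1% | 56.4% |
| 0.7 | 49% | 15% | 45.1% | 66.0% | 73.0% |
| 0.8 | 64% | 10% | 45.1% | 82.8% | 86.5% |

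The difference detectable with 80% power is 0.76 SD for the raw comparison. Multiplying by √(1 − r²) gives 0.66, 0.54 and 0.46 SD.

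More than half of the variance is removed only if r² > 0.5, that is r above about 0.71, and only against a raw follow-up comparison. At r = 0.3 the saving against raw follow-up is 9%.

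**5. Chance age imbalance.** The age distribution is not given. If ages were uniform over 6 to 84 months (assumed), the SD would be 78/√12 = 22.5 months. The standard error of the difference in mean age would be 22.5 × √(2/36) = 5.3 months at 36 per arm, so 95% of randomisations would fall within about ±10.4 months. A gap above 6 months would occur in about 26% of them. With 30 per arm the figures are 5.8 months, ±11.4 months and 30%.

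**The case against.** **The planned tests are valid.** This stands. Under randomisation they keep their type I error and are unbiased on average, and chance imbalance is already reflected in the standard error. A reader might infer from the age range that the estimate will be biased. The documents do not support that: the effect is extra variance, and a displaced estimate only in the one trial that is realised.

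**The size is unknown.** This also stands. A reader might conclude that most of the attainable precision is thrown away. That needs r above about 0.71 and a test on raw follow-up scores. The documents give no r and no SD, and they leave the tested variable open. If change scores are tested, much of the gain has already been taken, and the remaining saving shrinks as r rises.

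**Some outcomes lie outside the calculation.** MRI and EEG are primary outcomes, but no numerical variable is defined for either, so no r can be assigned to them. GMFCS is ordinal and does not suit a linear model. Excluding severe spastic CP narrows the spread in severity by an unknown amount.

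**Balance by hospital cannot be judged.** A reader might infer that allocation ignores hospital. Section 2.9 is silent on this, and silence does not show it.

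**A separate analysis plan could add covariates.** It could, and their absence from an article would not by itself be a finding. But section 2.14 names the tests that will be used, and none of them is adjusted, so an adjusted analysis elsewhere would depart from this text. The point concerns that stated choice.

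**Conclusion.** The point holds as a precision gain of assumed size for the continuous outcomes, not as an error that invalidates the analysis. Section 2.14 commits the trial to the less efficient analysis although the baseline value and age needed for the better one are already collected. Under the assumptions listed, the gain runs from modest (r = 0.5) to large (r = 0.8) if follow-up scores are tested, and is a 10% to 25% variance saving if change scores are tested. Apart from the loss of a degree of freedom, ANCOVA is no less precise than either. Any further gain from age and hospital beyond the baseline value has not been quantified, because the documents offer no basis for it. Naming the model would also settle which variable is analysed.

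**What to change.** In section 2.14, for the continuous outcomes (Gesell, GMFM, WeeFIM, and any numerical MRI or EEG measure once defined):

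- Make the between-group analysis an ANCOVA, or a mixed model over the 3- and 6-month visits, with treatment as the effect and the outcome's own baseline value, age at entry and hospital as covariates.
- Report the adjusted difference with its 95% CI.
- Keep the t or Wilcoxon test as a sensitivity analysis, and say whether it uses the follow-up score or the change.

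Analyse GMFCS levels with a method suited to ordinal data.

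The mixed model would also use the 3-month value of a child who leaves before 6 months, in line with the commitment in section 2.6 to include data up to withdrawal. With baseline as a covariate, it gains nothing from a child who leaves before the 3-month visit.

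The cost is analysis wording and a few degrees of freedom. Baseline values are already scheduled, age and hospital are known at entry, and no further data or children are needed.

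### Section 2.14 uses the unequal-variance t test only if variances are found to differ; using it for every t test is safer and almost free (minor improvement)

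*Protocol article*

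**What the plan says.** Section 2.14 (Statistical methods) of the protocol article names three between-group tests. The first two come in one sentence with no criterion for choosing: "The Student t test or the Wilcoxon rank sum test will be used to analyze differences between the groups". The sentence before it sorts data into normal and non-normal, but only for descriptive summaries. The third test is conditional: "If there is heterogeneity of variance, then Satterthwaite corrected" t test will be used. No variance test or threshold is given. The significance level is a P value "≤ .05 will be considered statistically significant".

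Section 2.13 (Outcome assessment) fixes the visits: "Outcome will be assessed at baseline, 3 and 6 months after the start of treatment". Section 2.4 (Intended sample size) says "the estimated sample size for each group is 30", raised to 36 for an assumed 20% loss, giving 72 in total at 1:1.

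**The concern.** The Student t test pools the two variances. It is reliable when the arms are equal in size, or when the spreads are equal. It goes wrong when both differ: too many false positives if the smaller arm has the larger spread, too few if the larger arm does. The Satterthwaite version corrects for this.

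A rule that applies the correction only after heterogeneity has been found depends on a check that is weak at this sample size. When the check misses a real difference in spread, the uncorrected test is kept. At stake is whether the error rate stays at the stated 5% if dropout is uneven and spread differs between arms.

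A smaller, related matter is that the article does not say which outcomes get a t test and which get Wilcoxon, or that the choice will be the same at both follow-up visits.

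**Working it through.** **Inputs from the article.** Significance level 0.05; 36 per arm, 1:1; loss 20%. Section 2.4 assumes "92% and 63% for the treatment and the control groups, respectively, α = 0.05, and β = 0.2". Its 30 per group is reproduced by the two-sided arcsine formula (29.1, rounded up to 30); the usual two-proportion formula gives 32. Then 30 × 1.2 = 36. This confirms the scale of the trial but does not affect the point. Expected completers per arm: 36 × 0.8 = 28.8, about 29, or 58 in all.

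**Assumptions, because the article gives no figures.** Normal data with equal means; SD ratio 1.5; variance check Brown-Forsythe at 5%. If a normality check is also applied, it is Shapiro-Wilk at 5% in each arm, with Wilcoxon used if either fails. Two uneven splits of 58 completers are used: 33 v 25 (losses 3/36 = 8% and 11/36 = 31%) and 36 v 22 (losses 0% and 14/36 = 39%).

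**Step 1: how far the Student standard error is off.** True variance of the mean difference: V = s1²/n1 + s2²/n2. Student assumes, on average, P = [(n1−1)s1² + (n2−1)s2²]/(n1+n2−2) × (1/n1 + 1/n2).

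- 29 v 29, SD 1 and 1.5: V = P, so there is no bias in the standard error.
- 33 (SD 1) v 25 (SD 1.5): V = 1/33 + 2.25/25 = 0.1203; P = (32 + 54)/56 × 0.0703 = 0.1080. √(V/P) = 1.056.
- 36 (SD 1) v 22 (SD 1.5): V = 1/36 + 2.25/22 = 0.1301; P = (35 + 47.25)/56 × 0.0732 = 0.1076. √(V/P) = 1.10.
- 36 (SD 1.5) v 22 (SD 1): V = 2.25/36 + 1/22 = 0.1080; P = (78.75 + 21)/56 × 0.0732 = 0.1304. √(V/P) = 0.91.

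Dividing 1.96 by these ratios gives approximate Student error rates of 6.3%, 7.5% and 3.1% for the three uneven cases.

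**Step 2: the two-step rule, by simulation** (20,000 trials per row, Monte Carlo standard error about 0.15 points; rejection rates in %).

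| Arms (SD) | Always Student | Variance check only | Normality and variance checks | Always Satterthwaite | Variance check positive |
|---|---|---|---|---|---|
| 29 (1) v 29 (1) | 5.0 | 5.0 | 5.1 | 5.0 | 4 |
| 36 (1) v 22 (1) | 5.0 | 5.0 | 5.1 | 5.1 | 4 |
| 29 (1) v 29 (1.5) | 5.1 | 5.0 | 5.3 | 5.0 | 45 |
| 36 (1) v 36 (1.5) | 5.1 | 5.1 | 5.3 | 5.0 | 55 |
| 33 (1) v 25 (1.5) | 6.4 | 5.6 | 5.9 | 5.0 | 45 |
| 36 (1) v 22 (1.5) | 7.7 | 6.4 | 6.5 | 5.3 | 44 |
| 36 (1.5) v 22 (1) | 3.3 | 4.3 | 4.5 | 5.1 | 41 |

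Smaller runs of 4,000 to 6,000 trials gave 5.1-6.2% for the rule against 4.7-5.3% for always-Satterthwaite at 33 v 25, and 6.0-6.9% against 4.6-5.4% at 36 v 22, with the larger SD in the smaller arm.

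**Step 3: reading the table.** With 58 completers the check misses a 1.5-fold SD ratio in 55-59% of trials. With all 72 children retained it misses 45%. The rule removes about half of Student's excess error but not all of it. The always-Satterthwaite column stays within 5.0-5.3%. With balanced arms nothing material is lost: even at an SD ratio of 2:1 with normal data, runs at 30 v 30 and 36 v 36 gave 4.9% and 5.7% for the rule against 4.5% and 5.3% for Satterthwaite.

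**The case against.** The wording is conventional, and the conditions for drift are not in the article. It plans equal arms and one overall loss rate, and nothing suggests uneven loss; 36 v 22 needs no loss in one arm and 39% in the other, with unequal spread as well. Under the strict null that acupuncture changes nothing, both arms share one distribution, and the rule held 4.5-5.8% across normal and skewed shapes. All of this stands and limits the point to a minor one. It does not remove the point: the conditional rule is written in the article, so this is not detail left to an unseen analysis plan, and a stated threshold would leave the same weakness.

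Three stronger readings are tempting and not supported:

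- A reader might infer a large inflation of error when outcomes are skewed and differ in spread. Any such excess comes from moving to Wilcoxon, not from the variance check. It is an error only if the target is the difference in means. Wilcoxon's null of identical distributions is false in that case, and section 2.14 does not say that the mean is the target.
- A reader might infer that the plan picks a test afresh for each outcome and visit after a normality test. The article does not say so; normality is tied to the summaries, and its role in choosing the test is only implied. Any estimate of how often the test would switch rests on assumed checks.
- A reader might infer that dropping the variance check settles everything. It does not: the choice between t and Wilcoxon would still be open.

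**Conclusion.** The point holds as a minor improvement. The explicit variance condition in section 2.14 gives no benefit over always using the Satterthwaite test. It costs roughly 0.5 to 1.5 percentage points of excess error when the smaller arm also has the larger spread, and makes the test slightly conservative in the reverse case. With balanced arms, or with one common distribution, there is no material harm. These sizes assume normal data, an SD ratio of 1.5, uneven losses and checks at 5%, none of which the article specifies. Leaving the choice between t and Wilcoxon unassigned is a matter of clarity; no error rate is attached to it here.

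**What to change.** Replace the conditional sentence in section 2.14 with wording such as: 'Wherever a t test is used it will be the Satterthwaite (unequal-variance) t test, with no preliminary test of variance. For each outcome, the t test or the Wilcoxon rank sum test is assigned in advance by type of outcome, and the same test is used at 3 and 6 months.' Ordered categories such as GMFCS levels suit the rank test. For scored scales the choice is a trade-off: a t test keeps the question on means, while a rank test may have more power if scores are strongly skewed. The team should decide before seeing outcome data.

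The cost is two sentences. With equal SDs and an assumed true difference of 0.75 SD, simulated power was 80.4% for Student and 80.3% for Satterthwaite at 29 v 29, and 77.5% and 77.1% at 36 v 22. No change in sample size follows.
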